### Outcomes {12}

The use of pairwise randomisation means that the timing of the follow-up for each pair can be based on the completion of the bathing adaptations. For each randomised pair, participant follow-up data will be collected at three points: (1) 4 weeks after the intervention participant receives their bathing adaptation, (2) 4 weeks after the control participant receives their bathing adaptation or at 9 months (whichever is sooner) and (3) 12 weeks after the control participant receives their bathing adaptation, or at 12 months (whichever is sooner). For some participants recruited early in the study, data were collected 2 weeks before the planned installation date of the bathing adaptation in the control group participant, where possible; however, a protocol amendment was approved to remove this follow-up as the majority of participants were not completing this due to the dates of their showers being installed or difficulty getting the dates in time to schedule the follow-up. We will follow the majority of participants for 12 months; however, for the participants recruited at the end of the trial, we will follow them for 9 months (i.e., follow-up will continue for 9 months from the randomisation of the final participants).

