#### Primary outcome

The primary outcome is in physical health status, measured using the Physical Component Summary (PCS) score of the SF-36 [19, 20]. The SF-36 is a generic measure of perceived health status and quality of life, which can be used across a range of medical conditions and disabilities. Its selection is based on the inclusion of the physical functioning subscale and is informed by the findings from the BATH-OUT-1 feasibility study [10, 14] and consultation with our Public and Person Involvement (PPI) group. The primary analysis will compare the PCS score of the SF-36 between the two groups, excluding the group lacking the mental capacity to complete it. The primary endpoint is the first follow-up assessment, which is 4 weeks post-adaptation in the intervention group, to evaluate the effect of adaptation versus no adaptation. Data from later time points will be used to address the secondary objectives.

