## Assignment of interventions: allocation

### Sequence generation {16a}

Eligible, consenting participants will be randomly allocated 1:1 to either the intervention (expedited bathing adaptation) or the usual care control group using the York Trials Unit secure web-based randomisation system. We will use ‘pairwise’ randomisation, at the level of the participant. Randomisation will be stratified by the capacity to complete the primary outcome. For those strata where the participant can complete the primary outcome, the randomisation is also stratified by site and property tenure (owner-occupied, local authority owned, privately rented including private and social landlords as one group), and for those who cannot, it will be stratified by site only. Randomisation will be stratified in this way as the primary analysis will exclude the group that was identified as being unable to complete the primary outcome at randomisation, and also as the wait for bathing adaptation can vary across sites and property tenures. After two participants within the same strata are recruited, they will be randomised together such that one will be allocated to the intervention group and the other to the control group, in a random order. We will do this so that we can follow both members of the pair up at the same time post-receipt of their adaptation to reduce the confounding effect of time to assessment. This is not the same as ‘matched’ randomisation.

Depending on the speed of recruitment, there is a risk that eligible participants may be left waiting to be randomised until another participant is available to pair with them. We shall limit the time participants wait to be randomised by allowing some flexibility for them to be paired, for example, with someone from a different property tenure within the same site and capacity. If a participant has not been randomised 3 weeks after consenting, they will be paired and randomised with any other participant who has consented at the same site. If, after 6 weeks, a participant has not been randomised, they will be paired and randomised with any other participant who has the capacity and has consented at any site. For those participants who are deemed not able to complete the primary outcome, they may be randomised using simple randomisation—without a pair, should the time waiting for a pair be too long.

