## Data collection and management

### Plans for assessment and collection of outcomes {18a}

Data will be collected at the following time points for both members of each pair (please see Figs. 1 and 2): (1) 4 weeks after the intervention participant receives their bathing adaptation, (2) 4 weeks after the control participant receives their bathing adaptation, or at 9 months (whichever is sooner) and (3) 12 weeks after the control participant receives their bathing adaptation or at 12 months (whichever is sooner).

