## Statistical methods

### Statistical methods for primary and secondary outcomes {20a}

#### Statistical analysis

A detailed statistical analysis plan will be agreed upon with the joint Trial Steering Committee (TSC) and Data Monitoring Committee (DMC) prior to the completion of data collection. All analyses will be conducted using the principles of intention to treat (ITT), including all available randomised participants in the groups to which they were allocated, where data are available. Analyses will be conducted using two-sided statistical tests at the 5% significance level. The flow of participants through each stage of the trial will be presented in a CONSORT diagram. Baseline and outcome data will be summarised descriptively by treatment group and overall.

The primary analysis will compare the PCS score of the SF-36 [19, 20] between the two groups, excluding the group lacking the mental capacity to provide this, using a covariance pattern mixed linear regression model incorporating all post-randomisation time points, where effects of interest and baseline covariates are specified as fixed effects, and the correlation of observations within patients over time (random effect) is modelled by a covariance structure. The model will adjust for the treatment group, time, treatment group-by-time interaction, baseline PCS score and property tenure, with participant and site as random effects. Estimates of the difference between treatment groups in PCS scores will be extracted for all time points with a 95% confidence interval and *p*-value. The primary endpoint will be the treatment effect estimate at the first assessment time point (4 weeks post-fitting of the intervention participant adaptions) to evaluate the effect of adaptation versus no adaptation. We will also consider a linear regression analysis that compares data from the two groups taken 4 weeks after their shower adaptations have been installed (first follow-up for intervention group participants, second follow-up for those control group participants who have received their adaptation). This will allow us to investigate whether increased wait times impact the short-term effect of the intervention.

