### Methods in analysis to handle protocol non-adherence and any statistical methods to handle missing data {20c}

We anticipate that the amount of missing data will be relatively small as a researcher will be collecting the data from most participants. The impact of missing primary outcome data will be minimised to some extent by using the repeated measures model, which allows the inclusion of intermittent responders. PCS scores for complete and intermittent responders will be compared descriptively. The impact of missing data will additionally be assessed using multiple imputation by chained equations.

At the primary time point, there may be some non-compliance, e.g. participants in the intervention group who have not received their adaptation and some in the control group who have. We will summarise the time taken to receive the adaptations in each group and whether this was completed as per the protocol. The primary analysis will follow ITT, but we will conduct a sensitivity analysis using complier average causal effect (CACE) analysis to estimate the effect of the receipt of, rather than the offer of, the allocated treatment. A two-stage instrumental variable (IV) approach will be used using the randomised group as the IV.

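### Follow-up 1, the primary endpoint, is the only visit with no fallback date, so primary data exist only in pairs whose intervention member is fitted

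*Protocol article*

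**What the plan says.** Outcomes {12} fixes the first two visits for each pair at "4 weeks after the intervention participant receives their bathing adaptation, (2) 4 weeks after the control participant receives their bathing adaptation or at 9 months"; for the second visit the earlier date applies. The third is "12 weeks after the control participant receives their bathing adaptation, or at 12 months (whichever is sooner". Plans for assessment and collection of outcomes {18a} repeats the schedule, again with no fallback for the first visit. Primary outcome states: "The primary endpoint is the first follow-up assessment, which is 4 weeks post-adaptation in the intervention group".

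Two other sections depend on that visit. Statistical analysis {20a} promises: "All analyses will be conducted using the principles of intention to treat (ITT), including all available randomised participants in the groups". It means analysis as allocated, subject to data being available, and uses a mixed model over all post-randomisation time points. Section {20c} foresees non-compliance at the primary time point, naming "participants in the intervention group who have not received their adaptation and some in the control group who have", and plans multiple imputation and a complier average causal effect (CACE) analysis with randomised group as the instrument.

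The abstract caps follow-up at 12 months. Outcomes {12} shortens this to 9 months for late recruits.

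**The concern.** The visit that carries the primary endpoint takes place only if the intervention member receives the shower. If that person dies, declines, moves or is still waiting when follow-up ends, the schedule gives no date on which to assess either member. Non-receipt is a realistic prospect: section {11b} foresees people no longer wanting or needing the shower, and the Discussion reports longer waits in both arms. For a late recruit with 9 months of follow-up, a fitting after about month 8 leaves no room for a visit 4 weeks later.

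Three things are at stake.

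- **Contradiction.** Under the schedule, nobody in the unfitted intervention group described in {20c} can have a primary-time-point value.
- **Selection.** Intervention data at that time point depend on the participant's own receipt. Control data depend on the partner's receipt. The comparison drifts from the effect of being offered an expedited adaptation towards the effect among those who got one.
- **Loss.** Each untriggered pair costs two primary outcomes.

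**Working it through.** **Inputs from the protocol article.** Difference 4 points, SD 8, 80% power, 5% two-sided, 45% non-collection, 15% unable to give the primary outcome, total 272 (Sample size {14}); 1:1 pairwise allocation (Trial design {8}).

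**Assumed, because the documents give no figure.** Share *u* of intervention participants never fitted within follow-up: 10, 20 or 30%. Receipt is worth 4 points and non-receipt nothing. Within-person correlation is 0.6. People who would not be fitted have the same health as the rest (gap 0) or score 4 points lower (gap 4). The same share of controls is unfitted by follow-up 2. No control is fitted before follow-up 1, except in a 10% variant.

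**1. The schedule side by side.**

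| Visit | Trigger | Fallback |
|---|---|---|
| 1 (primary) | 4 weeks after intervention member fitted | none |
| 2 | 4 weeks after control fitted | 9 months |
| 3 | 12 weeks after control fitted | 12 months |

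**2. The plan's own figure.** A standardised difference of 4/8 = 0.5 needs 63 per arm (normal) or 64 (t-test). 126/(0.55 × 0.85) = 269.5 and 128/(0.55 × 0.85) = 273.8, so 272 reproduces. Evaluable: 272 × 0.85 × 0.55 = 127.2, or 63.6 per arm. SE = 8 × √(2/63.6) = 1.42, and power for 4 points is 80.5%.

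**3. Intention-to-treat target.** 4(1 − *u*) = 3.6, 3.2, 2.8.

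**4. What the observed follow-up 1 data estimate.** Let m_R and m_N be the untreated means of those who would and would not be fitted. Observed intervention mean: m_R + 4. Observed control mean, selected only on the partner: (1 − *u*)m_R + *u*·m_N. Difference: 4 + *u*(m_R − m_N). With gap 0 this is 4.0 at every *u*. With gap 4 it is 4.4, 4.8, 5.2 before baseline adjustment.

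**5. Simulation, 400,000 pairs, adjusted for baseline PCS.** The repeated-measures column is a missing-at-random estimate that also uses follow-up 2; follow-up 3 was not included.

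| *u* | Target | Observed follow-up 1, gap 0 / gap 4 | Repeated measures, gap 0 / gap 4 |
|---|---|---|---|
| 10% | 3.6 | 3.99 / 4.16 | 3.85 / 3.95 |
| 20% | 3.2 | 4.02 / 4.31 | 3.73 / 3.91 |
| 30% | 2.8 | 3.98 / 4.47 | 3.54 / 3.87 |

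Excess of the model over the target: 0.25–0.35, 0.53–0.71 and 0.74–1.07 points.

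**6. CACE first stage** (proportion fitted, intervention minus control). With everyone assessed it is 0.9/0.8/0.7. Among those assessed under the schedule it is 1.0 throughout, so intervention-arm non-receipt disappears. The CACE on observed data is then about 4.0 with gap 0 and 4.2/4.3/4.5 with gap 4, against a true effect of receipt of 4. With 10% of controls fitted early, the first stage among those assessed is 0.9, so the analysis can still be computed and still corrects for that.

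**7. Power**, Φ(δ/(8√(2/n)) − 1.96), with n per arm.
- Capped visit, 127 evaluable, δ = 3.6/3.2/2.8: 72/62/51%.
- Untriggered pairs lost on top of the 45%: evaluable 127.2(1 − *u*) = 114/102/89, δ = 4: 76/71/65%.

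The second row is power for the effect among receivers, not for the intention-to-treat effect.

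**The case against.** The strongest reply is that the planned analysis copes. The article limits intention to treat to available data, the model uses all post-randomisation visits, and multiple imputation is planned. Unfitted participants stay in the model through their baseline and the capped follow-ups 2 and 3, and because both members of a pair lose the visit, arm sizes stay balanced. This stands in part: it narrows the gap (3.85 against 3.99 at 10%, gap 0) but does not close it. Under the schedule, no unfitted intervention participant supplies a follow-up 1 value from which a missing-at-random model or imputation could learn.

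Second, {20c} hints at a working rule for assessing unfitted participants, which the full protocol or the two figures, none of them shown, may contain. That is possible. But the article states the rule twice, with fallbacks for the other two visits, so the sections still need reconciling.

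Third, the primary objective asks about adaptation versus no adaptation, so an effect among receivers might seem to be what is wanted. But when non-receivers are less well, the observed data give 4.2–4.5 against a true receipt effect of 4, because only the intervention arm is selected on its own receipt.

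Fourth, controls must also be alive, willing and reachable, so some of their own losses would offset the selection. That is fair, and it is a reason to treat the sizes as illustrative.

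**Conclusion.** The point holds. The primary visit has no fallback date, the schedule conflicts with {20c}, and followed literally it moves the primary estimate above the intention-to-treat effect promised in {20a}. On the stated assumptions the excess after the mixed model is about 0.3 points at 10% non-receipt, 0.5–0.7 at 20% and 0.7–1.1 at 30%. The direction follows from the schedule provided that receipt helps; the sizes depend on assumed non-receipt, health gap and correlation.

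A reader might infer more than the documents support:

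- **That follow-up 1 is unlimited in time.** It lacks its own limit, but total follow-up ends at 12 months, or 9 for late recruits.
- **That the intention-to-treat and CACE analyses cannot work.** Both can be run. The first is distorted; the second loses only its correction for intervention-arm non-receipt.
- **That participants randomised without a partner lose primary outcomes.** Sequence generation {16a} allows randomisation "without a pair, should the time waiting for a pair be too long" only for those unable to complete the primary outcome, whom the primary analysis excludes. Only secondary outcomes are affected.
- **That the whole 45% non-collection allowance (272 × 0.85 × 0.45 = 104 people) is untriggered pairs.** Sample size {14} does not say so. The resulting 82% overstatement (4 against 4 × 0.55 = 2.2) also ignores the mixed model.
- **That type I error could reach 39%.** This needs 30% one-sided loss, an 8-point deficit (a full SD), no offsetting control loss and no baseline adjustment.

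**What to change.** In Outcomes {12}, Primary outcome and {18a}, define follow-up 1 as 4 weeks after the intervention participant's adaptation or at a fixed limit from randomisation, whichever comes first. Set the limit no later than 9 months so that late recruits are covered. Then:

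- collect it from both members whether or not either is fitted, and from the remaining member if the partner has died or withdrawn;
- use that value in the intention-to-treat analysis, and define receipt for the CACE at that date;
- where it coincides with follow-up 2, state that the single assessment serves as follow-up 1 in the model;
- reconcile the wording of {20c} with this definition before analysis.

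The change is not free. The 9-month contact already exists only where the control has not been fitted early enough to bring follow-up 2 forward. With a control fitted at month 5, follow-up 2 falls at about month 6 and follow-up 3 at about month 8, so a 9-month visit is an extra contact. Some such pairs would compare an unfitted intervention participant with a fitted control; that belongs in an intention-to-treat analysis, and the CACE then accounts for it. The expected effect is smaller and power somewhat lower: about 72/62/51% at 10/20/30% non-receipt with 127 evaluable, against 76/71/65% to detect 4 points if untriggered pairs are lost.

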#### Primary outcome

The primary outcome is in physical health status, measured using the Physical Component Summary (PCS) score of the SF-36 [19, 20]. The SF-36 is a generic measure of perceived health status and quality of life, which can be used across a range of medical conditions and disabilities. Its selection is based on the inclusion of the physical functioning subscale and is informed by the findings from the BATH-OUT-1 feasibility study [10, 14] and consultation with our Public and Person Involvement (PPI) group. The primary analysis will compare the PCS score of the SF-36 between the two groups, excluding the group lacking the mental capacity to complete it. The primary endpoint is the first follow-up assessment, which is 4 weeks post-adaptation in the intervention group, to evaluate the effect of adaptation versus no adaptation. Data from later time points will be used to address the secondary objectives.

#### Secondary outcomes

All secondary outcomes are collected at baseline and each of the follow-up time points:Perceived mental health status measured via the Mental Component Summary score (MCS) of the SF-36 [19, 20].Number of falls (self-reported).Health and social care service use and associated costs (will be captured using a purposely designed and tested resource use questionnaire).Health-related quality of life using the EuroQol EQ-5D-5L [21].Social care-related quality of life using the Adult Social Care Outcomes Toolkit (ASCOT) [16].Perceived risk of falling (Short Falls Efficacy Scale) [22].Independence in bathing (bathing question of the Barthel Index) [23].Ability to manage personal activities of daily living (Barthel Index) [23]. This analysis will include those who could not complete the SF-36 at baseline.Perceived difficulty in bathing (0–100 scale).Incremental cost per quality-adjusted life year (QALY) gained.

#### Alternative participants

If a consultee opinion is obtained for participation in the study, the extent to which the participant will answer the questions will be determined on a case-by-case basis and will be facilitated wherever possible. Participants may have support from another person (who may or may not be the consultee) as appropriate and any such support will be documented. In some cases, it will be clear that the participant cannot provide answers to questions. Participants who lack the mental capacity to complete participant self-reported outcome measures will complete a shortened assessment battery with an alternative participant. This assessment battery will include only factual information regarding the participant and the alternative participant’s opinions. These participants will not complete the primary outcome measure and we have accounted for this in our sample size calculation. We will collect the following secondary outcome measures at the follow-up time points previously stated where feasible:Health-related quality of life using the EuroQol EQ-5D-5L Proxy Version 2 [24].Health and social care service use and associated costs (this will be captured using a purposely designed resource use questionnaire).Independence in bathing (bathing question of the Barthel Index) [23].Ability to manage personal activities of daily living (Barthel Index) [23].Number of falls.

### Participant timeline {13}

Participants will be enrolled in the study, and the baseline assessment completed, as soon as reasonably practicable after they have been referred to the housing adaptations service. The timing of outcome assessments is detailed in the previous section.

### Sample size {14}

Studies examining the utility of the SF-36 across different clinical conditions have estimated the Minimum Clinically Important Difference (MCID) to be between 3 and 7 points [25–27]. This trial is powered to detect a conservative MCID of 4 points for our target population of older adults with a range of clinical conditions. The standard deviation of the SF-36 PCS in BATH-OUT-1 at baseline was 8 [14]. To detect a standardised difference of 0.5 with 80% power and 5% two-sided alpha and allowing for up to 45% non-collection of primary outcome data, and the inclusion of up to 15% of participants who lack the capacity to provide the primary outcome (based on data presented in the December 2022 Trial Steering Committee meeting), we will aim to recruit a total of 272 participants.

### Recruitment {15}

Recruitment will initially be undertaken by local authorities. Potential participants will be approached by members of staff at the site. If the person consents to contact by a researcher, they will receive an information pack and a telephone call to provide more information about the study and will be recruited at this point if they wish to consent.

## Assignment of interventions: allocation

### Sequence generation {16a}

Eligible, consenting participants will be randomly allocated 1:1 to either the intervention (expedited bathing adaptation) or the usual care control group using the York Trials Unit secure web-based randomisation system. We will use ‘pairwise’ randomisation, at the level of the participant. Randomisation will be stratified by the capacity to complete the primary outcome. For those strata where the participant can complete the primary outcome, the randomisation is also stratified by site and property tenure (owner-occupied, local authority owned, privately rented including private and social landlords as one group), and for those who cannot, it will be stratified by site only. Randomisation will be stratified in this way as the primary analysis will exclude the group that was identified as being unable to complete the primary outcome at randomisation, and also as the wait for bathing adaptation can vary across sites and property tenures. After two participants within the same strata are recruited, they will be randomised together such that one will be allocated to the intervention group and the other to the control group, in a random order. We will do this so that we can follow both members of the pair up at the same time post-receipt of their adaptation to reduce the confounding effect of time to assessment. This is not the same as ‘matched’ randomisation.

Depending on the speed of recruitment, there is a risk that eligible participants may be left waiting to be randomised until another participant is available to pair with them. We shall limit the time participants wait to be randomised by allowing some flexibility for them to be paired, for example, with someone from a different property tenure within the same site and capacity. If a participant has not been randomised 3 weeks after consenting, they will be paired and randomised with any other participant who has consented at the same site. If, after 6 weeks, a participant has not been randomised, they will be paired and randomised with any other participant who has the capacity and has consented at any site. For those participants who are deemed not able to complete the primary outcome, they may be randomised using simple randomisation—without a pair, should the time waiting for a pair be too long.

